## Abstract

**Background:**

Postinfectious cough usually develops and persists following respiratory tract infection. The protracted cough is embarrassing and troublesome and significantly impairs daily life. However, the optimal treatment available for this condition is still not known. This study aims to investigate the efficacy and safety of a new Chinese herbal prescription, Zihua Wenfei granule (ZHWFG), in treatment of postinfectious cough (wind-cold invading lungs syndrome).

**Methods:**

This study is a prospective, multi-center, randomized, double-blinded, parallel group, placebo-controlled trial. A total of 216 adult participants with postinfectious cough will be enrolled from six study centers across China. All participants are randomly allocated to one of three parallel treatment groups: (1) 15 g of active ZHWFG three times daily, (2) 10 g of active ZHWFG plus 5 g of ZHWFG-matched placebo three times daily, and (3) 15 g of ZHWFG-matched placebo three times daily. The treatment duration is 14 consecutive days. The primary outcomes are cough resolution rate and cough relief rate. Secondary outcomes include time to cough resolution, time to cough relief, change from baseline in cough symptom score, cough visual analog scale value, traditional Chinese medicine syndrome score at days 7 and 14, and change of CQLQ from baseline to post-treatment as well as adverse events.

**Discussion:**

This trial may not only investigate the efficacy and safety of ZHWFG in the management of postinfectious cough (wind-cold invading lungs syndrome), but also add the evidence of Chinese herbal medicine in treatment of postinfectious cough and provide an alternative option for the management of postinfectious cough.

**Trial registration:**

ChiCTR1900022078. Registered on 23 March 2019. http://www.chictr.org.cn/showproj.aspx?proj=36547.

## Background

Postinfectious cough is usually categorized as subacute cough lasting for 3 to 8 weeks and is the most common cause of subacute cough responsible for approximate 40 to 50% cases [1, 2]. Postinfectious cough usually develops and persists following respiratory tract infection, accounting for 10 to 40% cases [3, 4].

Postinfectious cough is generally self-limiting and benign; however, the protracted cough may become embarrassing and troublesome, even impairing daily life. In this case, patients may seek for medication therapy. Antihistamines, inhaled or oral corticosteroids, and central acting antitussive agents were used to relieve the cough, but treatment failure during tapering, relapse after drug withdrawal, and potential side effects may be faced [2]. Montelukast, a cysteinyl leukotriene receptor antagonist, was also found to be ineffective in this setting [5]. Inhaled ipratropium and salbutamol may reduce the cough, but the effect was short-acting [6]. Therefore, a growing number of patients turn to complementary and alternative medicine for relieve of cough.

Postinfectious cough is generally defined as exogenous cough in traditional Chinese medicine (TCM). Based on clinical practice and TCM syndrome research, wind-cold invading lungs is the most common syndrome in postinfectious cough [7]. This syndrome is primarily characterized by cough, throat itchiness, a small amount of white phlegm, and chest tightness. The general TCM therapeutic principle is to clear away wind-cold and relieve cough and to warm the lungs and reduce the phlegm.

Zihua Wenfei granule (ZHWFG) is a new Chinese herbal prescription and manufactured by Yuekang Pharmaceutical Co., Ltd (Beijing, China). Table 1 lists the detailed formula. Pre-clinical pharmacodynamic experiments (unpublished data) demonstrated that it can relieve cough and wheeze and reduce phlegm, and it also had antiallergic, anti-inflammatory, and antibacterial effects. A pilot clinical trial showed that Zihua Wenfei Zhisou decoction could alleviate the cough and was safe in treatment of postinfectious cough (wind-cold invading lungs syndrome) [8].

**Table 1 Tab1:** Formula of Zihua Wenfei granule

Pinyin name	Latin name	Family name
Ziwan	*Aster tataricus L. f.*	Compositae
Kuandong	*Tussilago farfara L.*	Compositae
Shegan	*Belamcanda chinensis L.*	Iridaceae
GanJiang	*Zingiber officinale Rosc.*	Zingiberaceae
Mangguohe	*Mangifera indica L.*	Anacardiaceae
Jingjie	*Nepeta cataria L.*	Labiatae

The aim of this trial is to evaluate the efficacy and safety of ZHWFG in patients with postinfectious cough (wind-cold invading lungs syndrome) in a randomized, double-blind, parallel, placebo-controlled trial. In this study, the investigators hypothesize that (1) the proportion of patients whose cough completely resolve will be higher in the treatment groups, (2) the proportion of patients whose cough relieve will be higher in the treatment groups, and (3) ZHWFG will be safe.

## Design

This study is a prospective, multi-center, randomized, double-blinded, parallel group, placebo-controlled trial. The study has been authorized by China State Food and Drug Administration (Approval No. 2016 L05843). In addition, this updated version of trial protocol (version 1.1) has been reviewed and approved by Biomedical Ethics Committee of West China Hospital, Sichuan University (Chengdu, China) on 24 December 2018. Furthermore, this trial was registered with the Chinese Clinical Trial Registry (ChiCTR1900022078) on 23 March 2019. This study is funded by Yuekang Pharmaceutical Co., Ltd (Beijing, China). However, the funder has no input in the study design, future data collection and management, or data analysis and interpretation. A research assistant at each study center is scheduled to recruit patients from late March 2019 to April 2020. The flow chart of the trial is shown in Fig. 1.

**Fig. 1 Fig1:**
[figure not shown]
Study flow chart. ZHWFG, Zihua Wenfei Granule

### Patient population and setting

In this trial, postinfectious cough is defined as a persistent subacute cough following symptoms of an acute upper respiratory tract infection, lasting for 3 to 8 weeks. Patients with postinfectious cough usually complain of irritable dry cough or with a little mucous sputum and have normal chest radiograph. Patients with persistent subacute cough due to other causes, such as pneumonia, cough variant asthma, upper airway cough syndrome, eosinophilic bronchitis, gastroesophageal reflux cough, asthma, or an acute exacerbation of chronic bronchitis will be excluded [9, 10]. The detailed TCM diagnostic criteria of wind-cold invading lungs syndrome are listed in Table 2. A total of 216 patients of either sex, aged 18–65 years old, will be enrolled from four academic centers and two tertiary hospitals across China: (1) West China Hospital of Sichuan University, (2) the first Affiliated Hospital of Guiyang College of TCM, (3) Affiliated Hospital of Zunyi Medical University, (4) Fujian Province Chinese Medicine Research Institute, (5) Beijing Hospital of TCM, and (6) the first Affiliated Hospital to Henan University of TCM. A research assistant at each participating site takes charge of patient screening and recruiting. The strategies for achieving adequate participant enrollment to reach target sample size include the following: (1) searching patient waiting list from respiratory outpatient, (2) referral from other community hospitals, and (3) enrolling candidate patients through announcement in public. The detailed inclusion and exclusion criteria are presented in Table 3.

**Table 2 Tab2:** Diagnostic criteria for wind-cold invading lungs syndrome

Category	Symptoms or signs
Main symptom	Cough
Minor symptoms	① Throat itchiness, ② cough aggravated by wind-cold, ③ a small amount of white phlegm, ④ chest tightness
Tongue	Pale red tongue with thin and white coating
Pulse condition	Floating, tight, or normal pulse

Patients with main symptom+①+②+either of the other two minor symptoms+appropriate tongue and pulse condition can be diagnosed as wind-cold invading lungs syndrome

**Table 3 Tab3:** Patients’ inclusion and exclusion criteria

**Inclusion criteria**	
1. Diagnosis of postinfectious cough	
2. Wind-cold invading lungs syndrome in traditional Chinese medicine Zheng	
3. Cough duration of 3–6 weeks	
4.Baseline cough visual analog scale of 60 mm or more	
5. Aged 18 to 65 years old	
6. Voluntarily provide written and informed consent	
**Exclusion criteria**	
1. Cough caused by asthma, cough variant asthma, upper airway cough syndrome, eosinophilic bronchitis, gastroesophageal reflux cough, or any other concomitant conditions	
2. Patients with severe pulmonary diseases such as lung cancer, lung tuberculosis, or lung fibrosis	
3. Use of an angiotensin-converting-enzyme inhibitor in the last 2 months	
4. Current smokers or recent ex-smokers quitting smoking less than 3 months ago	
5. Patients with temperature of 37.3 °C or above	
6. FeNO > 30 ppb	
7. Bronchial provocation test positive	
8. Post-bronchodilator FEV_1_/FVC < 0.70	
9. Patients with chest X-ray abnormalities	
10. Patient with severe underlying cerebral, hematological, hepatic, or renal disorders or other diseases significantly affecting the survival and prognosis, such as AIDS or cancer	
11. Mental patients or legal disability	
12. ALT or AST > 1.5 times of normal upper limit, urine protein >+, serum creatinine abnormality, white blood cell count < 3 × 10^9^/L or > 10 × 10^9^/L, and neutrophil granulocyte> 80%	
13. Pregnancy or potential pregnancy or lactation	
14. Allergic constitution or known to be allergic to any component in tested drug	
15. Patients taking similar medications in the last 1 month or having participated or participating in another trial in last 3 months	

### Randomization and blinding

Randomization sequence will be created by an independent statistician. Randomization will be carried out in blocks of six using Statistical Analysis System. Participants will be stratified according to study center and randomly assigned in a 1:1:1 ratio. Active and placebo granules will be identical in terms of outer package, labeling, and outer appearance of the medication packs. Random assignment sequence is concealed on a sealed scratch card in each study center to be revealed only when a medical emergency occurs. A research assistant will enroll participants and assign them to interventions. Investigators, participants, and biostatisticians will be masked to treatment assignments during the whole treatment duration. Unblinding is permissible only when a serious adverse event (SAE) or emergency rescue occurs.

### Investigational medication

Both active ZHWFG and ZHWFG-matched placebo are manufactured and supplied by Yuekang Pharmaceutical Co., Ltd (Beijing, China) in compliance with the Good Manufacturing Practice. All medications are provided in identical appearance and packaged and labeled in a blinding manner. Each code corresponds to a unique medication assignment number according to randomization list. Each package contains 24 bags of 10 g active ZHWFG or ZHWFG-matched placebo and 24 bags of 5 g active ZHWFG or ZHWFG-matched placebo. The package will be distributed at visits 1 and 2. A clearly visible label on each package states “FOR TRIAL USE ONLY.” The label includes medication information regarding trial approval number, medication number, name, indication and function, dose and specification, dosage regimen, storage requirement, period of validity, and the provider’s name. A specified drug administrator will be independently in charge of receipting, storing, distributing, and retrieving the investigated drugs. All these processes must be recorded in a medication registration book. Figure 2 shows time schedule of enrolment, visits for participants, interventions, and assessments.

**Fig. 2 Fig2:**
[figure not shown]
Schedule of study procedures. BPT, bronchial provocation test; CQLQ, cough-specific quality of life questionnaire; FeNO, fractional exhaled nitric oxide; PFT, pulmonary function test; TCM, traditional Chinese medicine; VAS, visual analog scale; ZHWFG, Zihua Wenfei granule

### Interventions

Participants will be randomized to orally take one of the following three investigational medications: (1) 15 g of active ZHWFG three times daily (10 g/bag + 5 g/bag), (2) 10 g of active ZHWFG plus 5 g of ZHWFG-matched placebo three times daily, and (3) 15 g of ZHWFG-matched placebo (10 g/bag + 5 g/bag) three times daily. Participants will be required to take the first two bags of medications under observation just after enrollment, and then instructed to take the medications regularly for the next 14 consecutive days.

### Concomitant treatments and forbidden medication

Medications applied to treat the underlying diseases, such as diabetic mellitus and hypertension, are permitted. However, new use of angiotensin-converting-enzyme inhibitors for hypertension is not permitted. Any Western medication or other Chinese medicinal therapy which can relieve cough is prohibited during the study. Additionally, antibiotics are not allowed in this study. If the participants take any forbidden medication, they will be withdrawn. Any medication used in this study must be documented in detail in case report forms (CRFs), including name, dose, dosage regimen, indication, and treatment period.

### Intervention adherence and compliance

Researchers will take the following measures to improve drug adherence: (1) earnestly implementing informed consent regarding the potential benefits and risks, doing comprehensive and detailed explanation works to make the participants fully understand the significance and importance of medication use; (2) recording contact information of participants including landline and mobile phone, email, QQ, and WeChat as detailed as possible to keep them in touch; (3) arranging follow-up visits at their convenient time; and (4) reminding a visit 1 day in advance.

At visits 2 and 3, the specified drug administrator will record the number and detailed specification of medication received, taken, and returned. Medication compliance will be calculated as the actual taken amount of study medication documented in a participant’s daily diary divided by the total amount planned for the participant.

### Withdrawal and termination criteria

Participants may discontinue the study prematurely at any time for any reason. The investigators will be entitled to withdraw any participant because patients develop SAE or allergic reaction, experience condition worsening, loss to follow-up, or take forbidden medications.

The National Pharmaceutical Supervisory and Administrative Department can terminate the whole study for any reason. The investigators may terminate or suspend the study due to SAE, poor efficacy, or significant deviation from the protocol during the study. The sponsors can also terminate the study because of management issues or funding problems.

### Outcome measures

#### Primary outcomes

Cough resolution rate: the proportion of patients whose cough is completely resolved.

Cough severity will be self-rated using a validated continuous horizontal 100-mm visual analog scale (VAS), with 0 indicating “no cough” and 100 indicating “worst possible cough” [11]. VAS value of the past 24 h will be evaluated every night at about 8:00 pm during treatment. Complete resolution of cough is defined as a reduction of VAS value to less than 17 mm [12]. Cough resolution rate across groups will be compared at days 7 and 14.
2.Cough relief rate: proportion of patients who achieve cough relief.

Cough relief is defined as a reduction of VAS value by 50% or more from the baseline. Cough relief rate across groups will be compared at days 7 and 14.

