### Sample size calculation

The sample size was calculated on basis of cough relief rate, using PASS 11.0. Based on the pilot clinical observation of 144 patients with postinfectious cough [8], cough relief rate in active treatments was estimated to 70%, with a difference of 30% or more considering clinically significant. Setting a two-sided *α* of 0.05 and *β* of 0.15, the sample size was estimated to be 46 cases for each group. Additionally, this trial involves exploring the effect and safety of different dosage; the sample size for each group was set to 60 cases. Taking approximate dropouts of 20% into account, the number of participants recruited was estimated to be 72 per group. Therefore, a total of 216 patients will be recruited in this trial.

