### Statistical analysis

The full analysis set (FAS) includes all randomized participants who take at least one bag of ZHWFG and have follow-up data. If post-treatment follow-up data regarding the primary outcomes are missing, last observation carried forward method will be carried out to adjust for the missing data. Per-protocol set (PPS) includes patients in the FAS who comply with the protocol, are adherent to the assigned study medication, complete the visits and measurements, and have no other protocol violations. Efficacy analysis will be performed based on both FAS and PPS patients. Safety analyses include all randomized participants who take at least one bag of ZHWFG and have data for safety assessment.

An independent statistician will perform statistical analysis according to the statistical analysis plan using Statistical Analysis System (SAS) 9.4. Continuous variables will be expressed as mean (standard deviation) if the data are normally distributed, otherwise median (inter-quartile) alternatively. Categorical variables will be presented as frequency (percentage). Baseline analyses will be performed using analysis of variance or nonparametric tests for continuous variables, and chi-squared or Fisher’s exact tests for categorical variables, respectively. The primary outcomes will be analyzed using CMH-*χ*^2^ test with associated 95% confidence intervals. Time to cough resolution and relief will be analyzed using the Kaplan-Meier approach, and the difference across groups will be compared using the log-rank test. Changes from baseline to post-treatment in CSS, TCM syndrome scores, VAS, and CQLQ will be analyzed using analysis of covariance with associated 95% confidence intervals. A two-sided *P* value of 0.05 or less is considered statistically significant.

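### The three arms are compared across groups, with no dose-versus-placebo contrast named, so a significant primary test would not by itself show which dose, if either, beats placebo

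*Protocol article*

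**What the plan says.** - **Design (Abstract, Methods).** "All participants are randomly allocated to one of three parallel treatment groups": 15 g active, 10 g active plus 5 g placebo, and 15 g placebo, each three times daily. Allocation is 1:1:1, stratified by centre (Randomization and blinding).
- **Hypotheses (end of Background).** Both efficacy hypotheses have a direction: "the proportion of patients whose cough completely resolve will be higher in the treatment groups" and "the proportion of patients whose cough relieve will be higher in the treatment groups".
- **Primary comparisons (Primary outcomes).** "Cough resolution rate across groups will be compared at days 7 and 14" and "Cough relief rate across groups will be compared at days 7 and 14".
- **Tests (Statistical analysis).** "The primary outcomes will be analyzed using CMH-*χ*^2^ test with associated 95% confidence intervals". For time to resolution and time to relief, "the difference across groups will be compared using the log-rank test". One two-sided 0.05 threshold is given and is not tied to any contrast.
- **Sample size (Sample size calculation).** Relief under active treatment is put at 70%, "with a difference of 30% or more considering clinically significant". With two-sided alpha 0.05 and beta 0.15 this gives 46 per group. The number is raised to 60 because the trial also explores dosage, and to 72 for dropout.

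Nowhere does the article name a dose-versus-placebo contrast, a pooled-active contrast, a trend test, or a rule for following up a three-arm result.

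**The concern.** The hypotheses ask whether treated patients do better than placebo patients. A chi-squared or log-rank comparison of three arms asks whether all three are the same. Such a test has 2 degrees of freedom and no direction, and it responds to a difference between the two doses as readily as to a difference from placebo. It also has no single effect size for a 95% confidence interval to describe.

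At stake is what the trial may conclude. If the primary p-value comes from the three-arm test, a significant result leaves open which dose works. It can also arise mainly from high dose versus low dose, with neither shown to beat placebo. The article gives the dose question as a reason for enlarging the arms, so equal effects of the two doses cannot be taken for granted.

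**Working it through.** **Inputs.** From the article: three arms; relief 70% on active treatment; a 30-point difference, hence 40% in the comparator (inferred, because that section does not name placebo); two-sided alpha 0.05; power 85%; 46 per group, raised to 60. All rates other than 70% and 40% are assumptions. Centre strata are ignored. A dose is said to beat placebo when the two-sided pairwise p is below 0.05 in its favour (pooled z-test, no continuity correction).

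**1. The plan's own figure of 46.**
- Two groups, unpooled variance: n = (1.960 + 1.036)² × (0.7×0.3 + 0.4×0.6) / 0.3² = 44.9, so 45.
- Two groups, pooled variance: n = [1.960 × √(2×0.55×0.45) + 1.036 × √0.45]² / 0.09 = 47.8, so 48.
- Three groups, 2-df chi-squared test: 85% power needs noncentrality 10.92. For 70/40/40% the mean is 0.50, and the noncentrality per patient per arm is (0.2² + 0.1² + 0.1²)/0.25 = 0.24. So n = 10.92/0.24 = 45.5, that is 46.

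The figure 46 is plausible under either kind of test, so it does not reveal which comparison was sized.

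**2. One possible result.** Take 33, 19 and 24 responders out of 60 (high, low, placebo: 55%, 32%, 40%).

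| Comparison | Chi-squared (uncorrected) | p |
|---|---|---|
| Three arms, 2 df | 6.88 | 0.032 |
| High vs placebo | 2.71 | 0.10 |
| Low vs placebo | 0.91 | 0.34 |
| High vs low | 6.65 | 0.010 |

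The three-arm test is significant, neither dose is shown to beat placebo, and the signal comes from the contrast between doses.

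**3. How often this happens.** Simulation at 60 per arm, at least 400,000 trials per row.

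| Assumed rates, high/low/placebo (%) | Three-arm test significant | Low dose beats placebo | Of significant three-arm results, neither dose beats placebo |
|---|---|---|---|
| 70/70/40 | 95% | 92% | about 0% |
| 70/55/40 | 86% | 39% | 0.3% |
| 70/40/40 | 94% | 3% | 4% |
| 55/40/40 | 38% | 3% | 20% |
| 55/30/40 | 71% | 0.1% | 48% |

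The second row shows the ordinary problem: the three-arm test is usually significant, but the low dose usually cannot be claimed. The last two rows show the more serious one, where the result supports neither dose.

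**4. Power of pairwise contrasts, 70% vs 40%.** Power = Φ{[0.3√n − z × √(2×0.55×0.45)] / √0.45}.
- n = 60: 92.1% at alpha 0.05 (z = 1.960) and 86.7% at alpha 0.025 (z = 2.241).
- n = 57 (72 less 20% is 57.6): 90.7% and 84.7%.

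**The case against.** The strongest reply is that the article never calls its primary test a global one. Under Primary outcomes, the phrase about groups accompanies the time points and names no test. The Statistical analysis section names the CMH test without that phrase. Only for log-rank, which serves secondary outcomes, are test and phrase joined. The promise of confidence intervals even suggests that between-arm estimates are intended, and the unshown analysis plan may list the pairs. All of this is fair, and it means that a definite 2-df primary test cannot be attributed to the sponsor. It does not remove the point. The article states a comparison for each primary outcome, and that comparison does not match its hypotheses. If pairs are meant, neither the pairs nor their alpha is given. Either reading leads to the same correction.

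Two stronger readings are tempting, and the documents do not support them.
- A reader might infer that 46 per group proves the trial was sized for two groups. Two-group formulas give 45 to 48 and a three-group test at 70/40/40% gives 46, so the number does not discriminate.
- A reader might take the 94% significance at 70/40/40% as a rate of false claims. It is mostly power for a high dose that truly works: in 96% of those significant results at least one dose beats placebo. It would mislead only if someone read it as evidence for the low dose, which the article does not plan to do.

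It is also fair that sensitivity to dose fits the stated interest in dosage, so the three-arm and dose-versus-dose comparisons need not be discarded.

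**Conclusion.** The point holds in this form: the comparisons as worded do not test the stated hypotheses, and the confidence intervals are promised without a contrast. A significant three-arm result would not by itself show which dose, if either, beats placebo.

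The size depends on the true effects. If both doses reach 70% against 40%, practically no significant three-arm result would lack a dose that beats placebo. At 70/55/40% the three-arm test has 86% power, against 39% for low dose versus placebo. At 55/40/40% about one significant result in five supports neither dose, and at 55/30/40% nearly half. These figures rest on assumed rates, 60 evaluable per arm, one endpoint at one time point, and no centre stratification. This should be corrected before unblinding, but it does not invalidate the design.

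**What to change.** State high dose versus placebo and low dose versus placebo as the primary contrasts. For each, give a centre-stratified 1-df CMH test and the centre-stratified risk difference with its 95% confidence interval. For the time-to-event outcomes, use pairwise log-rank tests of each dose against placebo. Say how the two contrasts share alpha, by a fixed order or a split. Keep the three-group comparison and high versus low dose as supportive analyses.

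The cost is wording in the protocol and analysis plan, plus the alpha split or test order. No new data or patients are needed: at 60 evaluable per arm, even a split to 0.025 leaves about 87% power at 70% versus 40%, and about 85% if only 57 remain. This covers one endpoint at one time point. Two primary outcomes at two time points raise a separate multiplicity question, which these power figures do not cover.

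### Two nested primary outcomes, each compared at two days, are all judged at two-sided 0.05 with no decisive outcome or day and no success rule, so the 5% error level is not secured

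*Protocol article*

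**What the plan says.** - **Outcomes.** The abstract (Methods) states: "The primary outcomes are cough resolution rate and cough relief rate".
- **Days.** Under Primary outcomes, resolution carries the sentence "Cough resolution rate across groups will be compared at days 7 and 14" and relief carries "Cough relief rate across groups will be compared at days 7 and 14". Neither day is given priority.
- **Arms.** "All participants are randomly allocated to one of three parallel treatment groups": two active doses and one placebo, allocated 1:1:1. The hypothesis at the end of the Background is directional and refers to the active arms in the plural: "the proportion of patients whose cough completely resolve will be higher in the treatment groups". A parallel hypothesis covers relief.
- **Test and threshold.** Statistical analysis says "The primary outcomes will be analyzed using CMH" (a chi-squared test) and gives one two-sided rule for the whole trial: a P "value of 0.05 or less is considered statistically significant".
- **Analysis sets.** "Efficacy analysis will be performed based on both FAS and PPS patients". Neither set is called primary.
- **Sample size.** The calculation uses relief only and names no day. It takes 70% on active treatment, a 30-point difference, two-sided α 0.05 and β 0.15, and arrives at 46 per group. This is raised to 60 because dose is also explored, and to 72 for dropout. α is not divided.

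**The concern.** Which outcome and which day decide a trial is a protocol-level choice. This article makes that choice by declaring four outcome-by-day comparisons primary and giving all of them the same 0.05 threshold. It does not say whether a win on either outcome is enough or both are needed, and each answer has a cost.

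- If either is enough, the trial has several chances at a primary claim and the overall error rate exceeds 5%.
- If both are needed, the error rate is protected, but the power was calculated for relief only.

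The outcomes are also nested, so resolution is a stricter cut of the same scale and not independent confirmation. What is at stake is whether a positive report from this trial carries the 5% error that a reader will assume.

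**Working it through.** **1. The plan's own figure.** Inputs from Sample size calculation: 70% active and 70 − 30 = 40% placebo (derived), two-sided α 0.05, power 85%.

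- Pooled variance: n = [1.960·√(2·0.55·0.45) + 1.036·√(0.7·0.3 + 0.4·0.6)]² / 0.30² = (1.379 + 0.695)² / 0.09 ≈ 47.8, so 48.
- Unpooled variance: n = (1.960 + 1.036)²·(0.21 + 0.24) / 0.09 ≈ 44.9, so 45.

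The stated 46 lies between these. It is therefore a two-group calculation for one outcome at one undivided 0.05.

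**2. Nesting.** Entry requires a baseline visual analog scale (VAS) value of at least 60 mm (Table 3), and resolution is a VAS below 17 mm. The fall is then more than 1 − 17/60 = 71.7%, and larger still from a higher baseline. Relief needs 50%. At a given day, every resolved patient is also relieved.

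**3. Number of tests in the FAS.**
- One three-group test per outcome and day: 2 × 2 = 4.
- Each dose against placebo: 2 × 2 × 2 = 8.

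With independent tests, the chance of at least one P ≤ 0.05 would be 1 − 0.95⁴ = 18.5% and 1 − 0.95⁸ = 33.7%. The tests are positively correlated, so these serve only as upper references.

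**4. Allowing for correlation.** The documents give no correlations, so they are assumed and varied. Trials with no treatment effect were simulated at patient level, with nested outcomes, a shared placebo arm, 58 to 60 patients per arm and day 7–day 14 correlations from 0.2 to 0.9.

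| Reading (any one P ≤ 0.05 counts) | Chance under no effect |
|---|---|
| 4 three-group tests, FAS | 15–17% |
| 8 dose-versus-placebo tests, FAS | 25–30% |
| Same 8, favouring active only (nominal 2.5%) | about 13–15% |
| Three-group tests, FAS and per-protocol set (PPS) both count | 21–23% |
| 16 dose-versus-placebo tests, both sets count | 33–40% |

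The rows that include the PPS assume that it holds 80–90% of patients.

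A second model worked on the test statistics themselves. It used a correlation of 0.5 between the two doses, which follows from 1:1:1 allocation. With the outcome and day correlations both set to 0.3, 0.5, 0.7, 0.8 or 0.9, the 8 FAS tests gave 30%, 28%, 24%, 21% and 17%. Only very strong correlation brings the rate below 20%, and even then it is more than three times 5%.

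**5. If both outcomes must succeed.** Joint power cannot exceed the smaller of the two single powers. The article gives no expected resolution rate, so joint power cannot be computed from it. The stated 85% is relief alone.

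**6. Power under a repaired rule** (70% v 40%, pooled formula).
- One decisive test at 0.05: 92% with 60 per group. With 72 × 0.8 = 57.6, so 58, it is 91%.
- α of 0.025 per dose: n = (2.241·0.7036 + 0.695)² / 0.09 ≈ 57.4, so 58 for 85% power. With 60 per group, power is 86.7%.
- Bonferroni over all 8 tests (0.05/8 = 0.00625 each): 77 per group for 85% power, which exceeds the 72 to be recruited. Power with 60 is 72.5%.

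**The case against.** The strongest reply is that the article condenses a fuller protocol and refers to an analysis plan that is not shown. Multiplicity adjustment, dose order and the primary analysis set commonly sit there. That stands for the analysis set and the dose order: their absence alone would not be a finding, and reporting the PPS beside the FAS is routine. It does not remove the main point. The two primaries, the two days and the single 0.05 threshold are stated in the article, and an analysis plan that adjusted for them would have to change the stated rule.

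Four further objections limit what may be said.

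- **Pairwise testing is inferred.** The article speaks of comparing rates across the groups and names a CMH test. One three-group test per outcome and day fits that wording. The plural hypotheses and the two-group sample size make dose-versus-placebo testing plausible but do not settle it.
- **No any-one-wins rule is stated.** The article says when a P value counts as significant, not which results support a claim. The two efficacy hypotheses are listed together, which could mean that both are needed.
- **Direction matters.** The hypotheses are directional, so a result favouring placebo is not a false efficacy claim. The relevant comparison is then 13–15% against 2.5%.
- **Part of the dose comparison is exploratory.** The sample size section says that the trial explores dosage. This softens the dose dimension but leaves the four outcome-by-day comparisons in place.

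**Conclusion.** The concern holds in a limited form. As written, the article does not secure a 5% error rate for its primary claim, because nothing says which of the outcome-by-day results decides and all are judged at 0.05.

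If any one result may support a claim, the chance of at least one false positive in the FAS is about 15–17% on the three-group reading and about 25–30% on the dose-versus-placebo reading. It is higher if PPS results count too. The size depends on assumed correlations, and very strong ones would bring the second figure down to 17–21%. If both outcomes are required, the error rate is not the problem, but the 85% power does not apply.

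A reader might infer that the false-claim rate is five times nominal across 16 tests, or that the plan allows any single win to count. The documents support neither. They fix no correlations, do not say that each dose is tested separately, and state no claim rule. Nor do they allow a figure for joint power, since no resolution rate is given.

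**What to change.** Before unblinding, state one decisive primary analysis. Relief at day 14 in the FAS is a natural candidate because the sample size rests on relief. Say whether the CMH test compares all three groups or each dose with placebo. Then control the 5% level over the two doses and the second outcome in one of two ways:

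- **Fixed sequence** at two-sided 0.05, stopping at the first non-significant step.
- **α split across doses**, 0.025 each (0.025 + 0.025 = 0.05), with resolution tested within a dose only after relief succeeds for that dose.

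Make day 7 and all PPS results secondary or supportive.

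This is a cheap improvement in wording and needs no extra patients. At 70% v 40%, the first step of a sequence has 91–92% power with 58–60 per group, and the split has about 87% with 60.

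The price is in claims. Isolated day-7 or PPS results can no longer be presented as primary. In a fixed sequence, a failed earlier step blocks everything after it. For example, if low-dose relief comes before resolution and fails, no resolution claim can be made for either dose. The sponsor should therefore choose the order deliberately.
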